### Sample size

A sample of 200 participants per group at 12 months will allow detection of a difference in smoking cessation rates of 8% between groups at 12 months (slightly smaller difference of 7% can be detected at 1 month), based on 5% smoking cessation in the usual care group and 13% in the intervention group, at 5% significance level and 80% power. This effect size is achievable and important from a population-effect perspective. Non-randomised and observational studies using less intensive smoking cessation interventions within disadvantaged groups have demonstrated high cessation rates [25,28-30]. Estimating that 30% of the sample are lost to follow-up (10% at each of one, six and 12 months), 290 patients per group will be recruited at baseline. The Centre receives approximately 50 new clients a week and 50% of those are for ongoing counselling care. All new clients will be eligible to complete the baseline touch screen computer survey. Over a 12-month recruitment period, 1,300 new clients will attend for counselling services. Staff estimate that 60%-90% of clients are current smokers. Assuming a median value of 75%, there will be approximately 975 eligible clients during the study period. Assuming a consent rate of 60% [28-31], 585 individuals will consent to participate in the study.

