#### Moderating factors

These items will be collected at baseline, used as part of the intervention print-out, and included in multivariate analysis. ***Sociodemographic characteristics ***will include age, gender, marital status, housing status, income, education, postcode. ***Nicotine dependence ***will be measured by the Heaviness of Smoking Index (HSI), a two-item short form of the Fagerstrom Tolerance Questionnaire [45]. The HSI scores range from 0-6 and are calculated by summing the points for 1) time to first cigarette smoked after waking (in minutes) and 2) number of cigarettes smoked per day. Higher HSI scores indicate more dependence on nicotine. ***Quit attempts***. A commonly used [16,17] item which asks "How many serious attempts to stop smoking have you made in the last 12 months? By serious attempt I mean you decided that you would try to make sure you never smoked again. Please include any attempt that you are currently making and please include any successful attempt made within the last year". ***Use of cessation aids***. Clients who have made a serious quit attempt will be asked about treatments they had used in their most recent quit attempt. A single item developed by Shiffman et al [16] will list various pharmacological, behavioural and alternative smoking cessation aids. ***Partner smoking behaviour***. One item [46] will assess partner smoking behaviour: "Does your partner smoke?" (response options: yes, yes but stopping with me, no ex-smoker, no never smoked, N/A). ***Depression***. A recent meta-analysis indicates that the Patient Health Questionnaire (PHQ) has sensitivity of 80% and specificity of 92% in diagnosing major depression [47]. The two-item PHQ2 is recommended by the US Preventive Services Taskforce for depression screening and will ask "Over the last 2 weeks have you felt down, depressed or hopeless?" and ".. have you felt little interest or pleasure in doing things?". ***Financial stress ***will be measured using a scale developed by Siahpush et al [9,48] and previously used as a predictor of smoking behaviour. It includes items asking "In the last six months, did any of the following happen to you because of a shortage of money?" followed by six options.

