#### Efficacy of intervention

To assess the efficacy of the intervention at smoking cessation (validated by expired air CO), the intervention and control groups will be compared on each of the primary outcomes using chi-square analysis: 1) proportion abstinent last 24 hours (validated) at one, six and 12 months; and 2) proportion abstinent for seven days at one, six and 12 months. Univariate analyses will be undertaken to examine factors associated with each of the two outcomes, using the chi-square test for categorical variables and the t-test or a non-parametric equivalent for continuous variables. In addition to the primary analysis, intention-to-treat analysis will also be undertaken whereby clients who fail to complete follow-up in the study will be considered to be continuing smokers. Multiple logistic regression analyses will be used to compare outcomes between the two intervention groups while adjusting for prognostic variables and potential confounders (sociodemographic, financial stress, depression, and other variables collected).

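### The supplementary adjusted logistic model is given about 13 baseline variables for about 36 expected quitters; if the intervention works, its odds ratio will tend to be modestly inflated

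*Protocol article*

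**What the plan says.** Three parts of the protocol article bear on this.

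- *Efficacy of intervention*: the primary outcomes are compared by chi-square tests at one, six and 12 months. Multiple logistic regression then compares the groups "while adjusting for prognostic variables and potential confounders (sociodemographic, financial stress, depression, and other variables collected". The list is open-ended.
- *Moderating factors*: "These items will be collected at baseline, used as part of the intervention print-out, and included in multivariate analysis". The sociodemographic items "will include age, gender, marital status, housing status, income, education, postcode", which is seven variables. Six further headings follow: nicotine dependence, quit attempts, use of cessation aids, partner smoking, depression and financial stress. Partner smoking has five response options.
- *Sample size*: 200 per group at 12 months, "based on 5% smoking cessation in the usual care group and 13% in the intervention group", "at 5% significance level and 80% power".

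The article gives no cap on the number of covariates, no rule for choosing among them and no penalised fitting method.

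**The concern.** In logistic regression the information comes mainly from the rarer outcome, here quitting. When there are only two or three events per estimated parameter, ordinary maximum likelihood pushes coefficients away from zero. If the intervention works, its adjusted odds ratio is then overstated.

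The adjusted model is a stated comparison of the groups. Because allocation is by whole weeks, readers may also turn to it for reassurance about baseline imbalance. An estimate that leans towards a larger effect serves that purpose poorly.

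**Working it through.** **1. The plan's own sample size.** With p1 = 0.05, p2 = 0.13, mean 0.09, two-sided 5% (sidedness is not stated, but two-sided reproduces the figure) and 80% power, without continuity correction:

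n = [1.960 × √(2 × 0.09 × 0.91) + 0.842 × √(0.05 × 0.95 + 0.13 × 0.87)]² / 0.08² = (0.793 + 0.337)² / 0.0064 ≈ 200 per group.

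The stated 200 is reproduced.

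**2. Expected events.** 200 × 0.05 + 200 × 0.13 = 10 + 26 = 36 quitters at 12 months. Using the recruited number after 30% loss, 290 × 0.70 = 203 per group and 203 × 0.18 = 36.5. Counting those lost as smokers, as in the intention-to-treat analysis, adds no events. At one month, 290 × 0.90 = 261 per group. The total is then 261 × 0.17 = 44 at 5% v 12%, or 261 × 0.18 = 47 at 5% v 13%.

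**3. Parameters (intercept not counted).** 7 sociodemographic + 6 other = 13 variables. With one parameter each plus treatment, there are 14. If partner smoking takes 4 parameters for its five options, there are 12 + 4 = 16, plus treatment = 17.

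**4. Events per parameter.**
- 12 months, 14 parameters: 36/14 = 2.6
- 12 months, 17 parameters: 36/17 = 2.1
- 12 months, 30 covariate parameters (assumed) plus treatment: 36/31 = 1.2
- One month, 14 parameters: 44/14 = 3.1 to 47/14 = 3.4

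**5. Effect on the treatment estimate.** Simulated trials of 400 (200 per arm) at 5% v 13% were fitted by ordinary maximum likelihood. Counts above 16 are assumptions about coding. Prognostic means a combined covariate SD of 0.8 on the logit scale, also an assumption. The excess is measured against the true conditional log odds ratio, so the shift from 2.84 to about 3.0 that adjustment itself causes is not counted as bias.

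| Covariate parameters | Covariates | True log OR | Mean estimate | Excess | 95% interval coverage |
|---|---|---|---|---|---|
| 0 | none | 1.043 | 1.063 | 2% | 96.1% |
| 13 | noise | 1.04 | 1.11 | 7% | – |
| 16 | noise | 1.04 | 1.14 | 10% | – |
| 25 | noise | 1.04 | 1.18 | 13% | – |
| 15 | prognostic | 1.098 | 1.210 | 10% | 93.9% |
| 20 | prognostic | 1.102 | 1.274 | 16% | 94.0% |
| 30 | prognostic | 1.101 | 1.353 | 23% | 92.6% |

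As odds ratios, the prognostic rows are 3.00 estimated as 3.35, 3.01 as 3.58 and 3.01 as 3.87. A separate run with 13 noise covariates gave a median odds ratio of 2.98 against 2.84. On the log scale that is 1.092 v 1.044, or about 5%.

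**6. Cause.** A Firth-penalised fit removed nearly all the excess. Its means were 1.10 to 1.11 against 1.10 for 15 to 30 prognostic parameters, and 1.02 to 1.05 against 1.04 for 13 to 25 noise parameters. This points to sparse-data bias of maximum likelihood.

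**7. No true effect.** With 9% in both arms (again 36 events) and 15 to 30 parameters, the mean log odds ratio was −0.01 to 0.01. The test rejected in 5.8% to 6.8% of trials. With 1,500 trials per setting, the simulation standard error is √(0.05 × 0.95/1500) = 0.6 points.

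**The case against.** The strongest reply is that coding, selection and fitting of covariates belong to an analysis plan that is not shown, and that the article never says all 13 variables enter one model. It speaks of analyses in the plural and of prognostic variables and confounders. The cessation-aids item is asked only of clients who made a serious quit attempt, so it could not enter a whole-sample model without recoding. This stands in part: the number of parameters is not fixed, and any figure beyond 13 to 16 is an assumption. But the article does more than stay silent. It commits the listed items to multivariate analysis and leaves the adjustment list open.

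Four stronger readings are tempting, and the documents do not support them.

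- *The adjusted effect will be biased whatever the truth.* With no effect the estimate is centred on no effect, so the model cannot create a direction.
- *The model will often fail to fit.* A failure rate of 19% arises with 5% in both arms and 25 parameters. That is 200 × 0.05 × 2 = 20 events and an assumed count. With 36 events and up to 30 parameters, about 1% of fits or fewer failed.
- *Postcode alone will use up the events.* That assumes raw postcode indicators, which the article does not specify.
- *The efficacy conclusion is undermined.* The primary comparison is the unadjusted chi-square test, which this leaves untouched.

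The univariate analyses are likewise not described as a screen for choosing covariates.

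**Conclusion.** The point holds in limited form. The listed covariate set is too large for about 36 events. If there is a true effect of the planned size, the adjusted odds ratio will tend to be overstated by about 5–10% on the log scale with 13–16 parameters.

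At 13 and 16 noise parameters the excess is 0.07 and 0.10. The unadjusted standard error is √(1/10 + 1/190 + 1/26 + 1/174) = 0.39, so the shift is about a fifth to a quarter of a standard error. Finer coding makes it larger, and interval coverage stays near 95%.

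This rests on the planning rates at 12 months, on reading the two passages together, on the simulated covariate structure, and on ordinary maximum likelihood. Event counts at one month are higher, and those for seven-day self-report may differ. The matter concerns the credibility of a supplementary estimate and is worth correcting because the correction is cheap.

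**What to change.** In *Moderating factors* and *Efficacy of intervention*, replace the blanket inclusion and the open-ended list with a small, prespecified set of baseline covariates expected to predict quitting. Heaviness of Smoking Index, age and recent quit attempts would be one example. With one parameter each plus treatment, that gives 36/4 = 9 events per parameter. Leave out raw postcode. If a fuller model is wanted, fit it with a Firth penalty and label it exploratory.

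This changes wording only; data collection and the primary test stay as they are. The downside is that the adjusted model accounts for fewer baseline variables.

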#### Acceptability

The proportion of participants reporting that the intervention was acceptable, useful, and effective will be determined with 95% confidence intervals.

## Discussion

Notwithstanding the challenges of research with hard-to-reach populations, well-designed randomised controlled trials are essential for testing hypotheses with strong theoretical underpinnings to produce high quality evidence. This study is significant in a number of ways. It targets a particularly vulnerable group in the population that has been resistant to anti-tobacco campaigns and strategies to date. The reduction of the social inequity in smoking rates is increasingly recognised as a priority by peak cancer and health organisations. Secondly, it will be the first methodologically stringent study to investigate the efficacy of a smoking care intervention with disadvantaged groups in Australia. Previous research in this area is marked by poor methodological design. Thirdly, the intensive, client-focussed approach to the intervention has the potential to produce an effect size higher than those reported in the international literature to date. In designing the intervention, the various interacting influences on smoking amongst disadvantaged groups were acknowledged. Finally, a setting readily accessible and acceptable to disadvantaged groups is being tested. If effective, the intervention has clear potential for implementation in standard care in community social services. This study will generate new knowledge in an area where the current information regarding the most effective cessation approach with disadvantaged groups is limited.

## Appendix 1

### Description of the content of the case-worker smoking cessation intervention sessions

#### Case-worker session 1

At the clients first visit during an intervention week, staff will receive the *survey print-out and checklist *alerting them to client smoking status, nicotine dependence, whether and how they have attempted to quit in the past and other issues such as depression or financial stress which may require additional support.

##### Encouraging a quit attempt

All clients will be advised to quit. West et al [49] have found that spontaneous quit attempts that involve a decision to cease immediately can be just as successful than those where planning and preparation have taken place. Staff are familiar with techniques such as *motivational interviewing *[40] to assist their clients in coming to positive decisions. At that initial visit, clients will be asked to sign a *behavioural *contract [50] outlining the support they will be given by staff to help quit smoking and their role in compliance with use of support strategies and making quit attempts.

##### Use of effective cessation support strategies

A major component of the intervention is the *provision of pharmacotherapy. *Evidence suggests that smokers from lower socioeconomic backgrounds have higher levels of nicotine dependence [3] and that pharmacotherapy is an essential component of cessation care [11]. Clients will be offered a choice of medication at no cost. Nicotine replacement therapy almost doubles the chance of quit success compared with placebo [18]. A simple, safe and user-friendly version of the Bittoun [25,26] algorithm for appropriate use of multiple NRTs will be offered to clients with high nicotine dependence. Local pharmacists will also be provided with the algorithm and suggested as a source of advice and monitoring. There is evidence that the ability to quit smoking and maintain cessation is influenced by social support [18,46]. The case worker will ask the client to nominate a *'support' person *for their quit journey and provide a *support pack *to give to their support person. The support pack will contain advice on support strategies (e.g. advice on supportive behaviour, committing to an attempt to quit together until successful, not smoking near them, an NRT discount voucher if a smoker, and the Quitline number). If a client does not have a potential support person, the caseworker will locate a volunteer at the Centre who will take on the role of the support person via telephone contact.

##### Support for other potential relapse-related factors

As relevant, clients will be provided with information about courses and support options offered by the centre and other local agencies for issues such as depression and financial stress.

#### Case-worker sessions 2

At the next visit, smokers who have attempted to quit will be asked about their progress.

##### Encouraging a quit attempt

Motivational interviewing will be used to encourage additional quit attempts among those who have tried and failed; and to encourage either an immediate or pre-planned quit attempt prior to the next session (within the next two weeks).

##### Use of Effective Cessation Support Strategies

Continued use of NRT will be encouraged. Clients will be advised about other medications available on prescription to maximise their chances of successful quitting including bupropion SR, and varenicline. They will also be provided with written materials to take to their doctor. Those who need further assistance such as *referral to specialised services *will be offered a fax or email referral to Quitline, whereby the Quitline will call them.

##### Support for other potentially relapse-related factors

Clients experiencing stressful situations (mental health, financial or relationship concerns), as recorded at the survey print-out will be offered enrolment into *Life Skills courses *provided by the Centre. Other support options in the local area will be discussed. There is evidence that individuals from lower socioeconomic positions tend to have greater needs for a variety of life stressors including housing needs, financial stress, employment concerns and physical and mental health concerns which affect relapse [9] They will also be offered the opportunity to schedule a visit together with their support person. At the final scheduled face to face meeting, clients will be asked to drop-in or phone-in when they require assistance. They will be told that their counsellor will make further phone contact to monitor progress and address relapse.

#### Phone contacts (× 2)

*Maintenance and follow-up *are important components of this intervention. When face to face visits finish, staff will phone clients and check on progress, address difficulties, identify needs and provide advice. If practical aids are required, the client will be asked to return to the clinic to collect them. The invitation of *un-scheduled drop-in or phone-in sessions *will be reinforced. Springett and Owens [51] note that a client-led approach which included a drop-in system where clients were not required to pre-book appointments was valued and acceptable to disadvantaged clients of a stop smoking service and increased retention to the program and in some cases quit rates.
